# ABBaH teens: Activity Breaks for Brain Health in adolescents: study protocol for a randomized crossover trial

**DOI:** 10.1186/s13063-021-05972-5

**Published:** 2022-01-06

**Keywords:** Physical activity breaks, Sedentary, Cerebral blood flow, Cognitive function, fNIRS

## Abstract

**Background:**

Physical activity breaks are widely being implemented in school settings as a solution to increase academic performance and reduce sitting time. However, the underlying physiological mechanisms suggested to improve cognitive function from physical activity and the frequency, intensity, and duration of the breaks remain unknown. This study will investigate the effects of frequent, short physical activity breaks during prolonged sitting on task-related prefrontal cerebral blood flow, cognitive performance, and psychological factors. Additionally, the moderating and mediating effects of arterial stiffness on changes in cerebral blood flow will be tested.

**Methods:**

This is a protocol for a randomized crossover study that will recruit 16 adolescents (13–14 years old). Participants will undergo three different conditions in a randomized order, on three separate days, involving sitting 80 min with a different type of break every 17 min for 3 min. The breaks will consist of (1) seated social breaks, (2) simple resistance activities, and (3) step-up activities. Before and after the 80-min conditions, prefrontal cerebral blood flow changes will be measured using functional near-infrared spectroscopy (primary outcome), while performing working memory tasks (1-, 2-, and 3-back tests). Arterial stiffness (augmentation index and pulse wave velocity) and psychological factors will also be assessed pre and post the 80-min interventions.

**Discussion:**

Publication of this protocol will help to increase rigor in science. The results will inform regarding the underlying mechanisms driving the association between physical activity breaks and cognitive performance. This information can be used for designing effective and feasible interventions to be implemented in schools.

**Trial registration:**

www.ClinicalTrials.gov, NCT04552626. Retrospectively registered on September 21, 2020.

**Supplementary Information:**

The online version contains supplementary material available at 10.1186/s13063-021-05972-5.

## Background

Implementation of classroom-based physical activity breaks is being considered as a potential solution to combating sedentary behavior among adolescents and improving cognitive function and scholastic performance [1]. Focus on adolescents is pivotal as they are among the least studied groups in relation to physical activity and cognitive performance [2, 3]. Additionally, in Sweden, adolescents spend about 10.3 h per day sedentary, and only 43% of boys and 23% of girls meet the physical activity recommendations [4]. However, previous research on the effects of physical activity breaks on cognitive performance in adolescents has been inconclusive, mainly due to heterogeneity in study designs and methodology [1, 5–9].

Particular focus has been given to executive functions [10], as they are potential prerequisites for successful learning [11], emotional regulation [12], and child development [13]. Furthermore, among the cognitive functions, enhancement from physical activity has been most evident in the executive functions [14]. Working memory is a core component of the executive functions and involves holding information in mind and manipulating it to meet task goals [15], but has not been often studied in relation to physical activity nor in younger populations [2]. There is a clear connection between adolescents’ physical activity and cognitive ability [5], but knowledge is lacking on which intensity, frequency, and duration of physical activity is necessary to influence physiological mechanisms important for brain health and function.

One important mechanism that may explain the effects of physical activity on cognitive performance is changes in blood circulation in the cerebral cortex, especially in the frontal lobe (prefrontal), which is involved in solving cognitively demanding tasks [16, 17], but the majority of research has been in adults. Generally, results have revealed that a single bout of exercise can elicit immediate cognitive task-related increases on cerebral blood flow post exercise cessation [18–22], but also decreases or no effects have been observed [23, 24]. Reasons for differing results are partly related to the moderating effects of timing, duration, and intensity of the physical activity, and the timing and type of cognitive test performed.

Frequent, short physical activity breaks may be a more feasible alternative than a single bout, to counter the negative effects of prolonged sitting during a school day [25]. Studies have demonstrated positive effects of frequent, short physical activity breaks on peripheral vasculature in adults and older adults [26–30], but effects on cerebral vasculature remain elusive, especially in adolescents. In adults, studies performed using frequent, short physical activity breaks have been inconsistent, showing positive, negative, and no effects on cerebral blood flow [31–34] and on cognition [35–38]. Decreases in cerebral blood flow, with favorable effects on cognitive performance, have been seen in adult populations and suggest a potential neural efficiency adaptation [23, 24, 39, 40]. This suggests that after performing physical activity, efficiency in performing the cognitively demanding task increases so that less resources are required [39]. However, it remains unknown if a similar adaptation occurs in adolescents. Furthermore, studies that have measured cerebral blood flow have used indirect measurement modalities, such as transcranial Doppler ultrasound. One study using a more robust modality—functional near-infrared spectroscopy (fNIRS)—to study cerebral blood flow, found that male children with autism spectrum disorders had significant beneficial effects of a 20-min physical activity bout, compared to a sedentary counterpart, on prefrontal task-related cerebral blood flow [41]. Although performed in younger children (ages 8–10), another study found that after intermittent or continuous exercise, prefrontal-dependent cognitive performance improved compared to the baseline measure and this was significantly explained by alterations in cerebral blood flow assessed using fNIRS [42]. With fNIRS, it is possible to monitor cerebral blood flow by measuring changes in the attenuation of near-infrared light passing through the cortical tissue. Because fNIRS is non-invasive and does not require a certain posture or setting as in functional magnetic resonance imaging (fMRI), it is often used for brain imaging studies in infants and children [13]. It is considered a more feasible and robust option to measure cerebral blood flow changes, particularly when used in conjunction with short-separation channels, to eliminate the contaminating signal from blood flow in other tissues [43]. There are yet no studies investigating the effects of frequent, short physical activity breaks on hemodynamic changes using this technique in adolescents. We believe that the use of short-separation channels will produce partly different results.

Earlier studies have mainly focused on the effects of physical activity breaks only on cognitive performance, neglecting the underlying mechanisms [1]. Two studies have compared how different frequencies and durations of physical activity breaks affect cognitive performance. One study in children found that two 20-min breaks of moderate intensity were better than one or none for cognitive performance [44]. The other study found that 10–20 min long moderate-to-vigorous aerobic bouts were more beneficial for cognitive performance than that of a shorter duration (5 min) [8]. Favorable effects on working memory, as well as on well-being, were also observed in a school setting with a 15 min self-paced physical activity break at intensities near maximal exhaustion (the “Beep test”) [45]. Although, according to the inverted-*U* theory, high-intensity physical activity can produce unfavorable effects on cognitive performance [14]. Moderate-to-vigorous intensity is most favorable on prefrontal cognitive performance, especially when measured immediately after exercise cessation [14]. However, one study of young adults found that breaking up prolonged sitting with a 6-min bout of high-intensity interval exercise had no effect on a prefrontal-dependent cognitive test [46]. Studies incorporating both cerebral blood flow and cognitive performance are needed. A study in adults found that frequent, short walking breaks of moderate-to-vigorous intensity had beneficial effects on working memory after 3 h of sitting, although, with a coinciding decrease in cerebral blood flow [40]. However, it was not significantly different from the uninterrupted sitting condition. Nevertheless, significant improvements were seen in mood and alertness after the walking break condition compared with the uninterrupted sitting [40]. Thus, physical activity breaks may improve psychological health in settings where prolonged sitting occurs, but requires investigation in adolescents and whether favorable effects can also be demonstrated for working memory performance.

In addition, physical inactivity has been found to negatively affect vascular health (arterial stiffness) even among children [47, 48], whereas physical activity breaks may counter these effects [49, 50]. Arterial stiffness can also affect the cerebral vasculature and may therefore moderate or mediate effects of breaking up prolonged sitting on task-related changes in cerebral blood flow.

Furthermore, for activities to be sustainable in a real-world school setting, they need to be inclusive and non-demanding, but also possible to be performed on a regular basis. We therefore sought to investigate the effect of such activities. In turn, the results can reveal not only the potential underpinning mechanisms related to physical activity and working memory performance, but also provide insight into the type, intensity, and duration of physical activity breaks that can be implemented in schools to improve learning and psychological well-being throughout the school day.

### Aims and research questions

The main purpose of this study is to investigate how 80 min of prolonged sitting with and without frequent, short physical activity breaks of different intensities affects fNIRS-measured cerebral blood flow (measured as changes in oxygenated hemoglobin [oxy-Hb]) in the prefrontal cortex, in an ecologically valid mimicked classroom setting, during working memory tests of differential mental workloads in 13–14-year-olds.

Our primary research question is:

How does oxy-Hb in the prefrontal cortex during a working memory test change from before to after 80 min of prolonged sitting and after 80 min of sitting with physical activity breaks; and do these changes differ between these 80-min conditions?

Our secondary questions are:
Do physical activity breaks during prolonged sitting affect cognitive performance on the 1-, 2-, and 3-back tests; and self-reported psychological factors (stress, mood, alertness, and sleepiness)? Are these changes significantly different between conditions?Are the changes in cognitive performance correlated with changes in oxy-Hb?Does baseline arterial stiffness (measured as augmentation index and pulse wave velocity) moderate the change in cerebral blood flow and cognitive performance?Does the change in arterial stiffness mediate the changes in cerebral blood flow and cognitive performance?

### Hypotheses

We hypothesize that:
Task-related increases in oxy-Hb will occur after the conditions involving physical activity breaks and will either stay the same or decrease after the prolonged sitting, and these changes will be significantly greater for the higher intensity break.Cognitive performance, specifically reaction time and accuracy on the n-back tests, will improve after the physically active conditions, but decrease or remain the same after the prolonged sitting condition. The changes will significantly differ between sitting with or without breaks of different intensities, such that more favorable changes will occur when the breaks are of higher intensity.There will be a correlation between changes in oxy-Hb and cognitive performance.Psychological factors, including cortisol-measured stress, and self-reported mood, alertness, and sleepiness, will improve after the physical activity break conditions, which will be significantly different from the prolonged sitting condition, where there will be no change.Arterial stiffness will be reduced after the physically active break conditions, and these changes will be different from the prolonged sitting condition, where no changes will occur or an increase will be observed.Changes in oxy-Hb will be mediated by changes in arterial stiffness.Baseline arterial stiffness will moderate the change in oxy-Hb and cognitive performance, such that there will be a more pronounced change in those with lower arterial stiffness.

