### Experimental conditions

To minimize physical activity on the morning of the visit, participants will be transported to the laboratory via taxi. On the morning of testing, participants will be asked to provide four saliva samples (for cortisol testing); immediately after waking up and at 30, 45, and 60 min thereafter. Once the participants arrive at the laboratory, a practice session of the cognitive tests will be performed, a saliva sample will be taken, and then a time-restricted, individually standardized breakfast (based on their food choices decided at the familiarization visit) will be provided. Participants at their initial visit will be advised to eat their preferred amount, which will be subsequently weighed and recorded. The portion sizes will be replicated at each visit. The activPAL activity monitor will be worn during the experimental conditions to monitor sitting time during the test day. Participants will be equipped with a chest strap heart rate monitor to be worn during the whole test day visit. After breakfast, pre-condition outcome measures will be collected.

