### Other measures

*Stress* will be measured using salivary cortisol concentrations. Saliva samples (collected during the first hour after waking up on test days, prior to breakfast, and before and after the 80-min intervention) will be centrifuged for 10 min at 4 °C at 2800 rpm, and subsequently frozen at − 80 °C. Concentrations will be measured using the ELISA kit Abcam, ab154996. Questionnaires on mood, alertness, and sleepiness that have been previously used in studies with adolescents will be filled-in while seated after fNIRS measurement and prior to the 2-min supine rest before the arterial stiffness measurement. *Mood* will be assessed using the Positive and Negative Affect Scale (PANAS) [70–72], which includes 10 positive and 10 negative affects. Participants will rate on a 5-point scale (very slightly/not at all; a little; moderately; quite a bit; extremely) the extent to which they experience that mood at the present moment. The positive affect adjectives include interested, excited, strong, enthusiastic, proud, alert, inspired, determined, attentive, and active. The negative mood adjectives include distressed, upset, hostile, irritable, scared, jittery, afraid, ashamed, guilty, and nervous. *Alertness* will be measured using a simple 10-cm visual analog scale (VAS) [73], going from “not at all” to “completely alert”. *Sleepiness* will be measured using the Karolinska Sleepiness Questionnaire (KSS) [74–76], where participants will rate on a 9-point Likert scale their current level of sleepiness going from “extremely alert” to “very sleepy, great effort to keep awake, fighting sleep”.

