### Statistical methods

Mixed effects models with subject as a random effect to assess within condition differences will be performed, and to examine time-by-condition interaction effects. Changes in arterial stiffness and PWV will be assessed in relation to cerebral blood flow changes in the mixed models.

Exploratory analyses will be performed excluding the short-separation regressors and ROI averages to compare to the main analyses.

Secondary outcomes (i.e., cognitive function, psychological factors, stress), will be assessed using mixed models, with the subject as a random effect, looking at both the within condition changes and the time-by-condition interaction effects. Correlational analyses will be performed to investigate the association between changes in cognitive function and cerebral blood flow if significant changes are seen. Maximum likelihood estimation will be used in the mixed models to handle missing data at random. Subsequent sensitivity analyses will be performed if necessary.

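### Cortisol-measured stress may be judged on its pre-to-post change within a condition, which carries any shared morning trend in full; the secondary question also mislabels this outcome as self-reported

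*Protocol article*

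**What the plan says.** The Hypotheses section predicts that "Psychological factors, including cortisol-measured stress, and self-reported mood, alertness, and sleepiness, will improve after the physical activity break conditions", and completes the sentence with "which will be significantly different from the prolonged sitting condition, where there will be no change". That makes three predictions: a fall after the active conditions, a difference from sitting, and a flat course in sitting.

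Under Statistical methods, "Secondary outcomes (i.e., cognitive function, psychological factors, stress), will be assessed using mixed models", with subject as a random effect and "looking at both the within condition changes and the time-by-condition interaction effects". Neither of the two readings is ranked above the other.

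Under Other measures, stress "will be measured using salivary cortisol concentrations". Samples are taken in the first hour after waking, before breakfast, and before and after the 80-min exposure. Under Experimental conditions, the waking-hour samples fall "immediately after waking up and at 30, 45, and 60 min thereafter". The same section puts the visit in the morning, with the pre-condition measures after breakfast.

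The secondary question under Aims and research questions asks about "self-reported psychological factors (stress, mood, alertness, and sleepiness". It asks first whether the breaks affect these outcomes, and then, separately, whether the changes differ between conditions.

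**The concern.** In each of the three conditions the second cortisol sample is later in the morning, and later after waking, than the first. Time since waking is therefore completely confounded with pre versus post. Randomising the order of conditions does not separate the two; only a comparison between conditions does. The design itself treats cortisol as moving with time, since it takes four timed samples in the first hour after waking.

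If cortisol drifts down over the window, a within-condition test can show a fall after SRA or STEP that owes nothing to the breaks. The same drift in SOCIAL would contradict the predicted flat course for a reason unrelated to sitting.

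There is a separate problem of labelling. The secondary question treats stress as self-reported, but the measurement section offers only cortisol for it, so the question as worded has no matching data.

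**Working it through.** The document states no figure for cortisol. Its only calculation, the sample size, is for oxy-Hb and is not an input here.

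**Inputs from the protocol article.** 16 participants; three conditions in crossover; an 80-min exposure; cortisol before and after it; a morning visit.

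**Assumptions, not in the document.** A cortisol fall of r = 5% to 15% per hour over the window; a shared decline of 0 to 1.0 SD of the change score; a two-sided 5% test.

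**1. Where a shared trend goes.** Write the mean change in condition c as τ + δ_c, where τ is the common time trend and δ_c the effect of the condition.
- Within-condition change: τ + δ_c. With no effect of the breaks this equals τ, not zero.
- Active minus SOCIAL: (τ + δ_active) − (τ + δ_SOCIAL) = δ_active − δ_SOCIAL. The trend cancels.

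**2. Size over 80 min.** The fall is 1 − (1 − r)^h, with h = 80/60 = 1.33 h.
- r = 0.05: 1 − 0.95^1.33 = 0.066.
- r = 0.15: 1 − 0.85^1.33 = 0.195.

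This is about 7-20% in every condition, SOCIAL included.

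**3. What a within-condition test does with it.** For a paired t-test at n = 16, with the same decline in all conditions and no effect of the breaks, the single-condition column is the exact rejection probability (noncentral t). The other two columns are simulated (40,000 runs; correlation of change scores between conditions 0 and 0.5).

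| Shared decline (SD) | One condition significant | Significant fall in SRA or STEP | Active-minus-SOCIAL contrast |
|---|---|---|---|
| 0 | 0.05 | about 0.05 | 0.049-0.050 |
| 0.3 | 0.20 | 0.32-0.36 | 0.049-0.050 |
| 0.5 | 0.47 | 0.64-0.71 | 0.049-0.052 |
| 0.8 | 0.85 | 0.95-0.98 | 0.051 |
| 1.0 | 0.96 | 0.99-1.00 | 0.050-0.051 |

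SOCIAL shows the fall as often as STEP. STEP significant with SOCIAL not significant, a pattern easily misread as an effect, occurs in 12-16% of null trials at 0.3 SD and 17-25% at 0.5 SD.

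Steps 2 and 3 can be linked only through the SD of the change in log cortisol, which the document does not give. On the log scale the fall is 0.068 to 0.217, so a decline of 0.5 SD corresponds to an SD of 0.068/0.5 = 0.14 up to 0.217/0.5 = 0.43. The table is illustrative.

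**4. The label.** Three places side by side:
- Aims and research questions lists stress among the self-reported factors.
- Hypotheses separates cortisol-measured stress from the self-reported items.
- Other measures gives cortisol for stress, and then "Questionnaires on mood, alertness, and sleepiness that have been previously used in studies with adolescents". These are PANAS, a VAS and the KSS; none is a stress instrument.

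**The case against.** The strongest reply is that the safeguard is already planned. The time-by-condition interaction is named for stress, the secondary question asks whether changes differ between conditions, and the hypothesis itself requires a difference from sitting. A decline shared by all conditions would make the full hypothesis fail. This stands. A reader might infer that the plan, followed as written, would declare that breaks reduce stress when they do nothing. The document does not support that, because the within-condition fall satisfies only one of the three predictions. What remains is that the article does not rank the interaction above the within-condition change, and asks separately whether the breaks affect stress.

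Second, the size of the trend is not in the document, nor are clock times. This also stands, so the percentages and rejection rates rest on assumption. A reader might enlarge the fall by placing the test batteries between the two samples. The article does not say that they lie there; it says that outcomes are collected immediately before and after each condition.

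Third, visits are made comparable by a consistent weekday, sleep and activity monitoring, matched dinners, taxi transport and a replicated breakfast. How the waking samples are used may properly be left to a fuller plan, and their absence from the model description is not held against the article. These measures support the between-condition contrast. They do nothing for the within-condition change.

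Fourth, the self-reported label may be a slip, since two other sections are clear. Agreed, but it sits in the research question, which is the sentence that results will be reported against.

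**Conclusion.** The point holds for a secondary outcome and for one of its two planned readings. Within-condition change in cortisol cannot separate an effect of the breaks from a common morning trend. Under an assumed 5-15% per hour, that trend amounts to about 7-20% over 80 min in every condition. The confounding follows from the design; its size and direction rest on the assumption.

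Two wider conclusions are not supported. The between-condition comparison is not biased by a shared trend, provided that time since waking is alike across visits. The primary oxy-Hb analysis is not touched.

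The label is a plain contradiction within the document and needs no assumption.

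**What to change.** For cortisol, state that conclusions rest only on the between-condition difference in pre-to-post change, SRA and STEP each against SOCIAL. Report the within-condition changes descriptively, and do not treat a flat course in SOCIAL as a test of the hypothesis.

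Preferably adjust the contrast for time from waking to sample. The timed waking samples and the diaries should supply it. This is worth doing because participants are tested in pairs with starts 20 min apart, and the article does not say that each keeps the same slot at every visit.

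In the secondary question, name salivary cortisol as the measure of stress and keep the self-reported label for the three questionnaire outcomes only.

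The cost is small: no new data, one analysis statement, one optional covariate and one corrected phrase. The price is one fewer within-condition claim. Recruitment is complete, so the hypothesis should stay on record as stated. The change in how it is judged should be dated and fixed before the cortisol results are examined.
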